**Aim 3. Patient-level clinical effectiveness**								
Proportion of Veterans who receive referrals (primary)	CDW	X		X	X	X		X
Facility-free days [54] (secondary)	GECDAC RHF	X		X	X	X		X
Hospitalization, skilled nursing facility utilization, functional status (secondary)	GECDAC Core Files, CDW	X		X	X	X		X

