**Fig. 2 Fig2:**
[figure not shown]
Flow Diagram for Adaptive Cluster-Randomized Controlled Trial. The figure shows the sequence of the four implementation periods, randomization, and cross-over allocation

In keeping with our operational partners’ interest in developing proactive approaches to identify high-risk veterans and intervene to prevent or delay functional impairment and associated acute care utilization, we will test the association of clinic-collected functional status measures with automated EHR-based frailty measures. Because frailty typically develops before functional impairment and may be a promising target for intervention [44–47], these findings will clarify how the two approaches might complement and inform one another.

Based on Primary Care and Office of Nursing Services capacity and input, we will implement the intervention in two waves, with 8 sites total. Sites may range in size depending on organizational capacity (e.g., a full community-based clinic or several primary care teams within a larger site). For both waves, we will cluster at the site level. Each site will move through three phases: Pre-Implementation, Implementation, and Sustainment (Fig. 3) [48].

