### Run-in period (standard implementation; 3 months)

We will implement the packaged intervention and local adaptations using the standard implementation strategy bundle (coalition building, implementation champions, local technical assistance, system-level audit and feedback). We chose this as the standard approach because its use resulted in 100% Reach in prior work and because use of champions (i.e., individuals who dedicate themselves to supporting and implementing an intervention) are associated with increased uptake of primary care interventions [55–57].

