#### Period 1 (Randomization to Standard or Enhanced Implementation; 3 months)

Our adaptive trial design will deploy resources to sites with the greatest need for enhanced implementation strategies [32–34]. After the Run-In period, data generated by the clinical screening tools (“Health Factors” data) will be used to identify sites with inadequate Reach, defined as < 80% of eligible veterans receiving LVN screening and/or PCP assessment (in keeping with standard benchmarks for adequate adherence to practice guidelines) [58]. We will define PCP assessment as reviewing LVN screening results and either (1) documenting via checkbox that further referral is not needed or (2) placing a referral to address identified impairments. We chose both LVN screening and PCP assessment as the benchmark for implementation response because these combined steps contribute to improved identification (via screening) and management (via assessment/referrals). Sites with ≥ 80% Reach at the end of the Run-In phase will receive the standard implementation bundle for all phases of implementation. For sites with < 80% Reach, we will randomize 1:1 by site to 3 additional months of standard vs. enhanced implementation. Based on current levels of functional status measurement in VA primary care practices (51% measuring function among ≥ 80% of eligible veterans), we anticipate that half of included sites (*n* = 4) will require enhanced implementation. The enhanced implementation strategy bundle will include the components of the standard bundle above (i.e., Coalition Building, Implementation Champions, Technical Assistance) plus clinician-level audit and feedback for participating LVNs and PCPs instead of site-level audit and feedback.

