#### Aim 3 (Clinical Effectiveness)

The primary outcome for Aim 3 is proportion of Veterans with impairments who receive appropriate referrals (Table 3). We will define appropriate referrals as the PCP reviewing the LVN screening results and either (1) documenting via checkbox that further referral is not needed or (2) placing a referral to address identified impairments. We acknowledge that management of functional impairment is complex and there is no “gold standard” for appropriate referrals. For example, a patient may not require a referral because they are already receiving services. Functional status assessment may also inform clinical decision-making (e.g., whether to order cancer screening) but not result in referral. Thus, we will capture clinician judgment of when referrals are appropriate. As noted above, we will use Health Factors data and clinical notes to capture clinician judgement of when referrals are appropriate.

Secondary outcomes include facility-free days, emergency department visits, hospitalization, short- and long-term skilled nursing facility (SNF) use, and functional status. Facility-free days measures the number of days a Veteran is alive and outside a hospital or SNF, calculated from GECDAC residential history files (RHF) [54]. The RHF integrates VA, Medicare (including Medicare Advantage), and Medicaid claims to describe episodes of care for individual Veterans in VA and non-VA settings [65]. We will assess other utilization with GECDAC Core Files [66] and functional status using CDW Health Factors data.

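### Table 3 schedules no run-in value for the Aim 3 referral outcome, although the run-in is the only period before randomisation in which that outcome can be measured on its own definition

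*Protocol article*

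**What the plan says.** All references are to the protocol article.

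- **Schedule.** Table 3 has columns Pre-Imp, R, P1, P2, P3, 3 M and 6 M. The Aim 3 primary row, "Proportion of Veterans who receive referrals (primary", has a mark at Pre-Imp, P1, P2, P3 and 6 M and none at R or 3 M. The two secondary rows, "Facility-free days [54] (secondary" and "Hospitalization, skilled nursing facility utilization, functional status (secondary", follow the same pattern.
- **Start of the tools.** Under the run-in heading: "We will implement the packaged intervention and local adaptations using the standard implementation strategy bundle". Table 1 (Component 3b) makes the clinician alert and referral menu part of that intervention.
- **Outcome.** The Aim 3 outcome section counts a veteran with impairment as appropriately managed if the primary care provider reviews the nurse screen and then either places a referral or records that none is required ("documenting via checkbox that further referral is not needed").
- **Randomisation.** It follows the run-in: "After the Run-In period, data generated by the clinical screening tools (“Health Factors” data) will be used to identify sites with inadequate Reach". Sites below 80% are randomised 1:1, and four are expected. The same section defines provider assessment by the same two routes as the Aim 3 outcome.
- **Baseline.** The pre-implementation section on measures and data says available data will supply baseline values for Tables 2 and 3.
- **Analysis.** The Aim 3 plan bases primary inference on standard versus enhanced, from logistic mixed models. It names no periods and no baseline term.

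**The concern.** The baseline that Table 3 schedules for the referral outcome precedes the tools that define the outcome. Both parts of the proportion are affected. The denominator is veterans whose impairment has been identified, which depends on the new two-step screen. The numerator includes a checkbox that belongs to the new template.

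The period that does supply a same-definition value before allocation, with every site on the same standard bundle, is the one left blank. With about two sites per arm, a chance difference between sites can be as large as a plausible strategy effect. A same-definition value from before randomisation is the direct way to see such a difference and adjust for it.

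**Working it through.** **1. Reading column R.** R is not in the table's abbreviations. It stands first among four implementation columns (R, P1, P2, P3). The Fig. 2 caption says "The figure shows the sequence of the four implementation periods, randomization, and cross-over allocation", and the text describes the run-in followed by Periods 1, 2 and 3. Run-in is an inference, but a firm one.

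**2. Which outcomes lack a comparable scheduled baseline.**

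| Aim 3 outcome | Source | Depends on the new tool? | Pre-Imp value comparable? |
|---|---|---|---|
| Appropriate referral (primary) | Health Factors, notes | Yes | No |
| Functional status | Health Factors | Yes, if from the new screener | Not in that case |
| Facility-free days | Residential history file | No | Yes |
| Hospitalisation, nursing-facility use | GECDAC Core Files | No | Yes |

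**3. Whether older screening data could fill the gap.** The Background says the earlier national screening covered ages 75 and older, with low and uneven uptake; this initiative covers 60 and older. The Aim 1 analysis plan compares sites by their type of pre-implementation measurement, so earlier practice differed between sites. Such data can describe sites but cannot reproduce the outcome.

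**4. What a run-in baseline could gain.** The plan gives no figure on this point. Let r be the correlation between a site's run-in and Period 1 proportions; the documents give none, so it is assumed. Adjusting for the run-in value scales the site-level variance by about 1 − r²:

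- r = 0.5: 1 − 0.25 = 0.75, a reduction of 25%
- r = 0.7: 1 − 0.49 = 0.51, a reduction of 49%
- r = 0.9: 1 − 0.81 = 0.19, a reduction of 81%

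For scale, take 2 versus 2 sites, the plan's design effect of 4.4, and an assumed proportion of 0.5 with m impaired veterans per site. The variance of a site proportion is 0.25 × 4.4 / m. The standard error of the arm difference is √[0.25 × 4.4 / m × (1 − r²) × (1/2 + 1/2)]. At m = 100 and r = 0 this is √0.011 = 0.105.

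| m | r = 0 | r = 0.5 | r = 0.7 | r = 0.9 |
|---|---|---|---|---|
| 50 | 0.148 | 0.128 | 0.106 | 0.065 |
| 100 | 0.105 | 0.091 | 0.075 | 0.046 |
| 200 | 0.074 | 0.064 | 0.053 | 0.032 |
| 625 | 0.042 | 0.036 | 0.030 | 0.018 |

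**5. Degrees of freedom.** A purely site-level comparison of four sites has 4 − 2 = 2 residual degrees of freedom, and 4 − 3 = 1 after adjusting for the run-in value. The two-sided 5% t quantiles are 4.30 and 12.71. The adjusted interval would be narrower only if √(1 − r²) < 4.30/12.71 = 0.338, that is r above about 0.94. A change from run-in keeps 2 degrees of freedom. Its variance factor is 2(1 − r): 1.0, 0.6 and 0.2 at r = 0.5, 0.7 and 0.9, so it gains only when r exceeds 0.5. A mixed model that also uses later periods lies outside these two cases and depends on its small-sample method.

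**The case against.** **The crossover already gives within-site information.** Sites first given the enhanced bundle return to standard in Period 2, and standard sites still below 80% Reach move to enhanced. Table 3 measures Aim 3 in Periods 1 to 3. This stands: a reader might infer that without the run-in value, site imbalance cannot be told apart from the strategy effect, and that would be too strong. The crossover contrasts are open to carry-over, however, and the standard arm's switch depends on its response, so they do not replace a baseline taken before randomisation.

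**Exclusion from the model is not stated.** This stands. A reader might infer from the blank column that run-in data are lost or will be left out of the analysis. The documents do not say so: the Aim 3 plan names no baseline, such detail may be in a fuller plan, and the data will exist because Reach is classified from them. What the article does fix is a schedule whose only pre-randomisation entry for this outcome is not comparable.

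**All Aim 3 outcomes share the blank cell.** For the utilisation outcomes this is no defect, because their pre-implementation values come from the same sources as later ones.

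**r may be low.** The run-in is the launch period, and randomised sites are selected on low run-in Reach, which shares the provider-assessment step. Either could weaken the correlation, so r = 0.7 to 0.9 may be optimistic. The figures are also on a linear site-level scale, while the planned model is logistic.

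**Conclusion.** The point holds for the referral outcome, and for functional status if it is taken from the new screener. The only pre-randomisation value that Table 3 schedules for them cannot be on the same definition as the later values, and the one period that could supply it is unmarked. It does not hold for facility-free days, hospitalisation or nursing-facility use.

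This is a gap in the schedule and in the stated baseline, not lost data or a comparison that cannot be made. The gain from closing it is protection against chance imbalance between sites and, if site levels persist, added precision: a site-level variance reduction of about 25% to 81% over assumed r of 0.5 to 0.9. With four sites, the interval does not shrink in proportion, because adjustment costs one of only two residual degrees of freedom in a site-level analysis. The conclusion rests on reading R as the run-in and on about four sites being randomised. The small number of sites remains the main limit in either case.

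**What to change.** 1. In Table 3, define R and mark it for the referral outcome, and for functional status where it comes from the new screener.
2. State that the run-in is the baseline period for the standard-versus-enhanced comparison, restricted to the randomised sites (below 80% Reach). In the logistic mixed model, constrain the arms to be equal at run-in and estimate the arm effect from Period 1.
3. Include site and site-by-period random effects. A site intercept alone would treat site differences as fully persistent and could understate the standard error. Alternatively, specify a site-level analysis that adjusts for the run-in value. Choose the form in advance, together with its small-sample degrees of freedom.
4. Use pre-implementation referral figures for description only. Keep the pre-implementation baselines for the utilisation outcomes.

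Cost: marks in one table column, a baseline period and a random-effect term in the model, and a sentence of text. The run-in extract is already needed to classify Reach, so sites and patients carry no added burden.

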### Description of intervention

The PACT Functional Status Screening Initiative includes four core components, which are described in detail in Table 1. Briefly, these components include: (1) routine, standardized measurement of functional status; (2) annual screening by a licensed vocational nurse (LVN) and follow-up assessment by a primary care provider (PCP); (3) electronic tools and templates to facilitate LVN screening, PCP assessment, and documentation; and (4) reports on functional status that can be tailored to the needs of different sites. The PACT Functional Status Screening Initiative will be implemented among veterans ages 60 and older in primary care settings. We chose this age cut-off because EHR frailty measures identified many younger veterans at risk for functional impairment, and this aligns with geriatrics and primary care priorities to proactively identify veterans at high risk for acute care and skilled nursing facility utilization.

**Table 1 Tab1:** PACT Functional Status Screening Initiative core components and rationale

1. Routine, standardized functional status measurement
• **Component 1:** Annual measurement with a standardized tool • **Rationale:** Addresses barriers to screening and assessment (competing priorities, lack of standardized processes) and to documenting and using data (lack of standardized data location, poor team coordination)

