**2. LVN screening and follow-up PCP assessment**
• **Component 2:** Annual LVN screening during patient triage and follow-up PCP assessment and referral(s), based on score • **Rationale:** Team-based approach clarifies team roles and responsibilities and fosters interprofessional environment

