**3. Electronic tools and templates to facilitate LVN screening, PCP assessment, and documentation**
• **Component 3a:** Validated LVN screening tool: (1) brief two-question pre-screener asking about difficulty performing ADLs and IADLs [41], and, among patients who report difficulty on pre-screener, (2) in-depth screener asking about difficulty and needing help with each ADL/IADL [42]. Results used to auto-populate nursing note • **Rationale:** Two-part screener intended to quickly identify patients who would benefit from in-depth screening while “screening out” individuals without impairment, reducing LVN and patient burden. Automation reduces documentation burden
• **Component 3b:** PCP alert and referral menu: If patient screens positive (i.e., reports difficulty/needing help with ≥ 1 ADL/IADL), PCP receives electronic alert linked to referral menu. Alert prompts PCP to review LVN screening results and perform additional assessment as needed. PCP can select up to 5 referrals: physical therapy, occupational therapy, social work, geriatric medicine, prosthetics; referral menus may be adapted at each site to meet local needs and include Community Care referrals • **Rationale:** Addresses clinical partner requests for integration of functional assessment into existing workflows and need for a standardized location to retrieve data on function; alert supports interprofessional approach to measurement; integrated EHR referrals address concerns that data will not be used to inform care and that clinicians lack knowledge of resources, making desired outcome (appropriate referral) more salient for PCPs

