#### Phase 3: Sustainment (6 months)

Implementation support will be withdrawn, and each site will transition to their Sustainment Plan. Implementation and effectiveness outcomes will continue to be evaluated (Tables 2 and 3).

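### Table 3 schedules functional status as an effectiveness outcome at P1, P2 and P3, but under the annual screen each veteran has at most one value in that phase, taken before the referral it prompts

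*Protocol article*

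**What the plan says.** All references are to the protocol article.

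- **Outcome and schedule.** Table 3, under Aim 3, has a row reading "Hospitalization, skilled nursing facility utilization, functional status (secondary"). It is marked at Pre-Imp, P1, P2, P3 and the 6-month Sustainment point, but not at Run-in or 3 M.
- **Source.** The Aim 3 outcome section states: "We will assess other utilization with GECDAC Core Files [66] and functional status using CDW Health Factors data". The Period 1 section explains that Health Factors are "data generated by the clinical screening tools". No separate or repeat functional assessment is described.
- **Frequency.** Table 1, component 1: "Annual measurement with a standardized tool".
- **Order of events.** Table 1, component 2: "Annual LVN screening during patient triage and follow-up PCP assessment and referral(s), based on score". Component 3b adds that after a positive screen the "PCP receives electronic alert linked to referral menu".
- **Timeline.** Screening begins in the 3-month Run-in. Periods 1, 2 and 3 last 3 months each, and the Implementation phase is given as 12 months. Sustainment adds 6 months, at the start of which "Implementation support will be withdrawn, and each site will transition to their Sustainment Plan".
- **Possible exception.** The Pre-Implementation section on barriers and adaptations names screening frequency as something sites might adapt. It fixes no interval and no site.

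**The concern.** An effectiveness outcome has to be measured after the intervention has had a chance to act. Here the outcome measurement is also the first step of the intervention: the screen produces the score, and the score prompts the alert, the provider's review and any referral. With a yearly screen and a 12-month phase, a value recorded in P1, P2 or P3 is normally the veteran's only one under the initiative, and it predates the referral.

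Two comparisons would then mislead. Across periods, each column contains whoever happened to be screened in that quarter, and people who attend often tend to be screened early. Between strategies, the enhanced bundle sends clinicians lists of their patients not yet screened or assessed, so it is designed to change who enters the data. In either case a difference in recorded function can arise with no veteran's function having changed. The article says Pre-Implementation measures serve as a baseline for later periods, so these columns are meant to be compared.

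**Working it through.** **1. Phase length.** Run-in 3 + Period 1 3 + Period 2 3 + Period 3 3 = 12 months, which matches the stated Implementation phase. Adding 6 months of Sustainment gives 18 months from launch.

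**2. When a repeat screen falls due.** Due month = month of first screen + 12.

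| First screened in | Months from launch | Repeat due in months | Position on the 18-month timeline |
|---|---|---|---|
| Run-in | 0–3 | 12–15 | Sustainment |
| Period 1 | 3–6 | 15–18 | Sustainment |
| Period 2 | 6–9 | 18–21 | after the end |
| Period 3 | 9–12 | 21–24 | after the end |

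On the core annual schedule no repeat falls due in P1 to P3. Only veterans first screened in months 0–6 can have one within the timeline.

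**3. Sensitivity to the interval.** The article gives no visit rates, so these are assumptions: random visits at 2 to 4 per year, with a due screen completed at 80% to 100% of visits. Simulated over 18 months:

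| Minimum interval | Veterans with two or more screens in months 0–12 | P1–P3 values that follow an earlier screen under the initiative |
|---|---|---|
| 12 months | 0% | 0% |
| 11 months | 1–5% | 2–11% |
| 6 months | 19–59% | 29–63% |
| 3 months | 34–80% | 45–77% |

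At the 12-month interval, 24% to 60% of veterans screened during Implementation have a repeat screen in Sustainment.

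**4. How far selection alone can move the columns.** All inputs here are assumed. Half the panel attends at a higher rate and half at a lower rate, and everyone is screened at the first visit. With quarterly visit rate r, the share first screened in quarter k (k = 0 for Run-in) is exp(−r·k) × (1 − exp(−r)). For 4 visits a year (r = 1) and 1 visit a year (r = 0.25):

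- Frequent attenders: 0.632, 0.233, 0.086, 0.031.
- Infrequent attenders: 0.221, 0.172, 0.134, 0.105.
- Frequent attenders as a fraction f of those first screened: 0.741, 0.574, 0.389, 0.231.

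Impairment among those screened = p_low + (p_high − p_low) × f:

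| Assumed visits per year | Assumed impairment, frequent / infrequent | Run-in | P1 | P2 | P3 |
|---|---|---|---|---|---|
| 4 and 1 | 30% / 10% | 24.8% | 21.5% | 17.8% | 14.6% |
| 4 and 1 | 20% / 10% | 17.4% | 15.7% | 13.9% | 12.3% |
| 4 and 2 | 30% / 10% | 22.3% | 19.9% | 17.4% | 15.3% |
| 4 and 1 | 20% / 20% | 20.0% | 20.0% | 20.0% | 20.0% |

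No veteran changes in any row. Over the columns Table 3 actually marks (P1 to P3), the fall is 21.5 − 14.6 = 6.9 points in the first row, 3.4 in the second, 4.6 in the third and nil in the last. This shows a mechanism and is not a forecast.

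**The case against.** Several points on the other side are fair.

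- **Screening frequency may be adapted locally.** This stands as a qualification. A site on a 6-month interval would produce many post-referral values in P1 to P3. But no such interval is fixed, annual measurement remains the core component, and Table 3 marks the columns for all sites.
- **Some veterans were screened before.** Annual screening of veterans aged 75 and over dates from 2009, and about half of practices already measure function widely. For these veterans a P1 to P3 value is not the first ever recorded, and a Pre-Imp value is a usable baseline. Even so, the later value precedes the initiative's own referral.
- **Drift over time affects both strategies.** True: falling columns do not by themselves bias the standard versus enhanced contrast. That contrast has a separate problem, since the strategy itself changes who is screened.
- **The detail may sit in an analysis plan.** The article itself fixes the outcome, its source, its timepoints and the screening interval. The conflict is among these, so this is not an omission.

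Two stronger readings are tempting and are not supported. A reader might infer that a fall in recorded impairment would be reported as clinical benefit. The article never says so, and its hypothesis is increased identification and better management. A reader might also infer that the 5% missing-data rule forces imputation of screens not yet due. It offers multiple imputation only as an example, alongside complete-case analysis, and does not say that such values count as missing.

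**Conclusion.** The point holds in qualified form. On the article's core annual schedule, functional status at P1, P2 and P3 consists of at most one value per veteran, taken before the initiative's own referral and from different veterans in each column. It cannot serve there as a measure of effect on function; period or strategy differences largely reflect who was screened. The conclusion rests on a 12-month interval. It is nearly unchanged if annual tolerates 11 months, and it weakens only at sites that choose a clearly shorter interval.

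The scope is limited. Functional status is one of several secondary outcomes. The primary referral outcome, facility-free days, and the hospitalization and nursing facility use that share the row are not affected. The 6 M column can hold post-referral values for some veterans, so the outcome is partly recoverable. The change should be made, but the trial's main conclusions do not depend on it.

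**What to change.** 1. In Table 3 and the Aim 3 text, separate functional status from the utilization measures, and label its P1, P2 and P3 values as descriptive case-mix and not an effectiveness outcome.
2. Define the effectiveness outcome as within-veteran change from the first screen under the initiative to the repeat annual screen in Sustainment (the 6 M column). This will come mainly from veterans first screened in months 0–6.
3. Keep Pre-Imp values, where they exist, as a baseline or covariate.
4. State that a screen not yet due is not missing for the 5% rule.
5. Report the change as an observational pre-post result and not as a randomised standard versus enhanced contrast. Being screened is affected by the strategy, and the arms are no longer separated by the time of the repeat screen. Non-responding standard sites cross to enhanced in Period 2 while enhanced sites return to standard, all sites are on standard in Period 3, and support is then withdrawn.
6. If a site adopts a shorter screening interval, record it and report that site's repeat values separately.

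The cost is wording in one table and one section, with no new data collection. The drawback is that only veterans screened early who return by month 18 contribute: about 24% to 60% of those screened in Implementation under the assumed visit rates. They may differ from those who do not return.
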